### Part 2: Stepped-wedge trial

#### Study population

Residents of 18 Queensland RACFs with at least 50 residents at their facility.

#### Inclusion criteria

Registered RACFs within Queensland, Australia, with at least 50 residents; able to provide the monthly de-identified reports necessary to conduct the study.

#### Exclusion criteria

RACFs with fewer than 50 residents; RACFs unable to provide monthly de-identified study reports.

#### Randomisation of RACFs

The 18 RACFs will be randomly assigned to an intervention starting time in a stepped-wedge RCT. The trial will be conducted across a 20-month observation period. The first month will be a control period for all sites; one site will transition from control to intervention each month for 18 months based on their randomisation; the final month will be an intervention period for all sites.

#### Control period (1–18 months)

Whilst in the control period the RACF will deliver usual care, which involves the facility’s current processes in relation to antibiotic use and the stewardship programmes.

#### Transition period (1 month)

This period will be the time when the intervention will be established by engagement of facility staff, delivery of educational materials to registered nurses and GPs and implementation of protocols and digital resources from the AMS ENGAGEMENT bundle.

#### Intervention period (1–18 months)

Whilst the RACF is in the intervention period it will receive a set of multimodal and multidisciplinary services, the ‘AMS ENGAGEMENT’ bundle, summarised in Fig. 2 and described in Table 2. The intervention will be delivered at the level of the RACF.

**Fig. 2 Fig2:**
[figure not shown]
The AMS ENGAGEMENT bundle intervention components

**Table 2 Tab2:** Key elements of the RACF AMS ENGAGEMENT bundle

Intervention components	Activities	Delivery and phase
Education and engagement of (a) GPs and pharmacists (b) Nurses (c) Residents and their families	Develop information packages on (a) Antibiotic choice and duration (b) Indications for specimen collection, notification of infection-related symptoms to GPs and microbiological testing as clinically indicated (c) Hazards of inappropriate use for RACF residents and families	A 4-week course for RACF nurses with a primary focus on treatment of suspected UTIs. Brochures and posters for residents and families. Academic detailing with GPs. **Induction** to be implemented during the transition period from control to intervention (online-only delivery possible if required) **Maintenance** materials for refresher training and/or new employees available during intervention
Nursing initiatives to enable seamless delivery of the trial	Establish a dedicated telehealth portal (using messaging and telephone communication) to enable RACF nurses to communicate with a researcher team member (on an as-needs basis) with regard to any aspect of the trial.	Phone, email and BlackBoard Web Platform®—using online discussion forums to communicate with an expert member of the research team. **Induction and maintenance**
Guideline development specific to antibiotic use in RACF residents	Evidence-based resident-specific clinical pathways and antimicrobial guidelines will be collaboratively developed with input from emergency clinicians, infectious diseases/microbiologists, geriatricians and general practitioners	State guidelines will be tailored to RACFs based on knowledge of local practices, reviewed annually. **Induction and maintenance**
Antimicrobial stewardship team creation in RACFs	Establish an AMS team at each facility. The composition of this team will include the clinical nursing director of the RACF, infection control nurse, a key GP working in the RACF, a pharmacist from the pharmacy providing quality use of medicine services to the RACF and an antimicrobial steward.	Oversee the stewardship process, review of the antibiotic guidelines for the RACF, review of the suite of interventions which are part of package and review of outcomes. Members of research team will participate in the first two AMS meetings to build capacity. **Induction and maintenance**
Emergency department liaison and promotion of state-wide clinical pathways to ensure consistency of practice across the care continuum	Establishment of an ED liaison to ensure continuity of AMS practices across health care settings	RACF staff to communicate with an ED liaison via phone and /or a letter informing them of the resident’s participation in the trial and key goals of AMS ENGAGEMENT **Induction and maintenance**
Electronic decision support to guide RACF urine testing and GP antibiotic prescribing	Access to mobile technology that provides decision support to underpin antibiotic use among RACF residents.	Access to QH Management of Acute Care Needs of RACF residents Guidelines App to help with diagnosis and prescribing and decision-making. **Induction and maintenance**
Telehealth support for key intervention components	Quarterly webinars with an expert panel on key issues related to AMS and/or practice changes in RACFs	Telehealth to support case discussions, and for education and training. AMS team and expert panel from research team to act as a panel with three monthly teaching sessions and case-based discussion open to all RACF-registered nurses and GPs in the intervention period **Induction and maintenance**

*AMS* antimicrobial stewardship, *GP* general practitioner, *QH* Queensland Health, *RACFs* residential aged care facilities, *UTI* urinary tract infection

#### AMS ENGAGEMENT Bundle Needs Assessment Toolkit

An AMS Needs Assessment Toolkit (NAT) will be developed and refined based on consultation with RACF clinical staff, reviews of the literature and published resources. Existing materials will inform its design, including the Clinical Excellence Commission’s Antimicrobial Stewardship Progress and Planning Tool (for acute care in Australian hospitals but modified for use in the aged care setting) [38] and the Centres for Disease Control and Prevention: “Core Elements of Antibiotic Stewardship for Residential aged care facilities” [39]. The NAT will assess the following points:Whether the RACF has the necessary resources for AMS (i.e. staff and methods) to establish clinical governance (current prescriber/General Practitioner (GP) involvement in the stewardship programmes). If an AMS programme exists, explore how the trial can enrich and support this service.Whether suitable institutional policies and procedures exist for antibiotic prescribing and administration, in particular with regard to treating suspected UTIs.What UTI management practices take place at the facility (e.g. symptom identification, diagnostic work-up, diagnosis, treatment, administration of treatment, review, communication).How antibiotic consumption and antibiotics-related adverse events and resistance patterns are identified, tracked and reported.

Each RACF will use the information collected from the NAT to determine key areas for focus and collaboratively develop an action plan prior to implementation, e.g. availability and use of an Imprest Medication System, GP and nurse knowledge on national and local antibiotic guidelines, processes related to urine testing (e.g. use of dipsticks), staff and family member awareness and education on AMR and its prevention. RACFs will also determine the best approach for access to specialist medical advice, monitoring and methods for reporting of AMS metrics.

The NAT will be emailed to the site coordinator ahead of the first AMS workshop and the responses will inform the discussions in the first AMS workshop for each facility. The findings of the NAT will help with refinement and implementation of the AMS ENGAGEMENT intervention bundle that each facility implements during the stepped-wedge trial.

Three months prior to a RACF’s randomised intervention start date, the research team will communicate with the facility to start the process of establishing an AMS clinical governance team (and if one already exists, they will receive support and mentoring from the research group and their resources will be enriched using trial material). This team will be assembled to discuss the NAT in an initial AMS workshop and identify how best to operationalise the interventions within their facility. Based on the NAT results, appropriate interventions will be selected from the AMS ENGAGEMENT bundle at each facility (Fig. 2).

Given that a single intervention is unlikely to be effective in stewardship programmes, nor in care improvement processes at RACFs [40], this trial will deliver a set of multimodal, multidisciplinary interventions to optimise antibiotic use in RACFs. This RACF *AMS ENGAGEMENT* bundle will comprise the following key interventions, which will be informed by the NAT and individual requirements of each facility (Table 2):*E*ducation and engagement of prescribers, nurses, pharmacists and residents and family members*N*ursing initiatives to improve UTI diagnosis and reduce inappropriate urine testing*G*uideline development specific to antibiotic use in RACF residents*A*ntimicrobial stewardship team creation in RACF with *G*P involvement*EM*ergency department liaison and use of clinical pathways to ensure consistency of practice across the care continuum*E*lectro*N*ic decision support to guide RACF urine testing and GP antibiotic prescribing*T*elehealth support for key intervention components

The study has been designed to allow the remote delivery of all intervention components (i.e. through use of print materials, videoconferencing, webinars, telephone support and electronic bulletins).

The Trial will involve the implementation of an AMS ENGAGEMENT bundle into 18 RACFs using a stepped-wedge-RCT design (Fig. 3).

**Fig. 3 Fig3:**
[figure not shown]
Schematic representation of the stepped-wedge AMS ENGAGEMENT study

### Outcome measures

#### Primary outcome measure

The primary outcome measure for this trial is antibiotic use as measured by DDDs of antibiotics per 1000 resident bed days.

#### Secondary outcome measures

Number of urine samples collected per 1000 resident bed days between the control and intervention periodsPercent susceptibility of Enterobacteriaceae to ceftriaxone, ciprofloxacin, cephalexin and amoxicillin-clavulanateAll-cause year-on-year mortality rates of RACF residents between the control and intervention periods (per 1000 resident bed days and median rate across facilities)Number of RACF residents admitted to hospital during the control vs intervention periods (per 1000 resident bed days and median rate across facilities)Number of cases of *C*. *difficile-*associated diarrhoea between the control and intervention periods (per 1000 resident bed days and median rate across facilities)The net cost of the intervention.

#### Exploratory outcome measures

Barriers and enablers to improving AMS practices in RACFs.

This study will also report outcomes in relation to most of the recently published Core Outcome Set for antimicrobial stewardship [41]. Antibiotic dispensing and resident data reported by RACFs will enable calculation of the total number of antimicrobial courses prescribed that are actually dispensed (incidence of antimicrobial use) per 1000 resident bed days; and days of therapy per 1000 resident bed days (rate of antimicrobial therapy). Infection-related mortality will also be reported (using before and after antibiograms). Appropriateness of antimicrobial prescribing will not be reviewed. No restrictions will be imposed on facilities for undertaking other education or activities related to medication prescribing and optimisation outside of the ENGAGEMENT bundle (e.g. routine facility pharmacist in-service sessions).

### Sample size

Sample size was calculated based on the outcome of antibiotic consumption as measured by DDDs. For a trial to run over 20 months with a mean cluster size of 50 residents and a control event rate of 120 DDDs per 1000 resident days [22, 42], 18 RACFs will provide 82% power to detect a 20% reduction in DDDs, which has been demonstrated as feasible by other studies [28, 43] (although these studies have utilised other metrics to quantify antibiotic consumption). The power calculation is based on a conservative intra class correlation coefficient (ICC) of 0.012 and coefficient of variation of 0.3 [44].

### Statistical analysis

The primary outcome is DDDs of antibiotics per 1000 occupied bed days. DDDs will be measured at the patient level monthly and analysed using a generalised linear mixed model for count data. The model will include fixed effects for intervention (AMS ENGAGEMENT vs control) and calendar time (randomised crossover times) and two random effects, one for variation among RACFs and a second to accommodate repeated measures over time on participants. Analysis will be by the intention-to-treat-schedule; that is, calendar time in the statistical model will be the randomised crossover times irrespective of whether crossover actually occurred at the pre-specified time. If there are discrepancies between randomised and actual crossover times, a supporting analysis will use the actual time that crossover occurred. Results will be expressed as rates per 1000 occupied bed days with 95% confidence intervals.

Data from the transition months will be reported but not included in the final analysis. All data will be analysed using SAS software (SAS Institute Inc., Cary, NC, USA). For the primary analysis, a *P* value less than 0.05 will be considered statistically significant. A statistical analysis plan will describe in detail the pre-specified analysis for all efficacy and safety outcomes and be available in the public domain before database lock.

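### The calendar-time fixed effect is defined as the randomised crossover times; read literally, this removes the adjustment for secular trend and conflicts with the stated power

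*Protocol article*

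**What the plan says.** All of the model text is in the Statistical analysis section of the protocol article.

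- Outcome and model: "DDDs will be measured at the patient level monthly and analysed using a generalised linear mixed model for count data".
- Fixed effects: "The model will include fixed effects for intervention (AMS ENGAGEMENT vs control) and calendar time (randomised crossover times) and two random effects". The random effects are "one for variation among RACFs and a second to accommodate repeated measures over time on participants".
- The intention-to-treat sentence repeats the definition of time: "calendar time in the statistical model will be the randomised crossover times irrespective of whether crossover actually occurred at the pre-specified time".
- If actual and scheduled dates differ, "a supporting analysis will use the actual time that crossover occurred".
- "Data from the transition months will be reported but not included in the final analysis".

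The schedule is in Randomisation of RACFs: "The trial will be conducted across a 20-month observation period", and "one site will transition from control to intervention each month for 18 months based on their randomisation". Month 1 is control for every site and month 20 is intervention for every site.

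The Sample size section gives 18 RACFs, 20 months, 50 residents per cluster, 120 DDDs per 1000 resident days, a 20% reduction, ICC 0.012, coefficient of variation 0.3 and 82% power.

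**The concern.** In a stepped wedge every cluster is observed first under control and later under intervention. Any background change in antibiotic use is therefore mixed with the intervention effect unless the model has a term for the period of observation. That term must vary within a facility from month to month.

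A facility's crossover time does not vary. With one site crossing per month, its 18 values simply label the 18 facilities. As a factor it is aliased with the facility effect; as a number it is a facility-level covariate. Under either coding nothing in the model tracks the month.

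The intention-to-treat principle belongs to the exposure indicator, which says whether a facility-month counts as control or intervention by the randomised schedule. The calendar month is the same whether or not a site crossed on time, so it needs no such rule. The text has attached the rule to the wrong variable.

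The article itself gives reasons to expect background change: a ten-year rise in consumption (Background), COVID-19 (Challenges: retention of sites), and other prescribing activities left unrestricted (Exploratory outcome measures). It does not quantify the effect of any of these over the trial.

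**Working it through.** **1. Calendar gap.** Label the facilities k = 1 to 18 by crossover order. Facility k has control months 1 to k, transition in month k+1 (excluded), and intervention months k+2 to 20.

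- Mean control month: (k+1)/2
- Mean intervention month: (k+22)/2
- Difference: 21/2 = 10.5 months for every k

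Across all facilities there are 171 control and 171 intervention facility-months, centred on months 6.7 and 14.3.

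**2. The plan's own figure.** I used the generalised least squares variance for a stepped wedge with a random facility intercept. Inputs from the Sample size section: 18 facilities, 20 months, 50 residents per cell, 0.120 against 0.096, ICC 0.012. Transition cells are dropped. My assumptions: rates treated as proportions, variance averaged over the two arms, two-sided 0.05.

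- Total variance: (0.12×0.88 + 0.096×0.904)/2 = 0.0962
- Between-facility variance: 0.012×0.0962 = 0.00115
- Cell error variance: 0.988×0.0962/50 = 0.00190
- Power = Φ(0.024/SE − 1.96)

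| Time term | SE | Power | Months of linear trend passed to the effect |
|---|---|---|---|
| Calendar month, categorical | 0.00837 | 81.8% | 0 |
| Periods cut at the set of crossover dates (months 19 and 20 merged) | 0.00837 | 81.8% | 0.007 |
| Own crossover month, linear or categorical | 0.00563 | 98.9% | 10.5 |
| No time term | 0.00554 | 99.1% | 10.2 |

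The stated 82% is reproduced with month effects. Setting the between-facility SD to 0.3×0.12 instead of using the ICC gives 81.1%. Other variance choices, with or without the transition month, give 72.9% to 87.0% with month effects and 96.8% to 99.4% with own-crossover time. The stated figure lies inside the first range and outside the second. Pure Poisson variation over bed days gives about 100% under every coding, so that variant does not discriminate.

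**3. Why own-crossover time gives 10.5 under both codings.** As 18 categories it absorbs all between-facility information. As a number it does the same, because a facility's share of intervention months is (19−k)/19, which is linear in k. Only the within-facility contrast remains, and its calendar gap is 10.5 months at every site.

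**4. Size of the bias.** Suppose a log-linear background change by a factor c from month 1 to month 20 (19 steps) and no true effect. The literal model then estimates a rate ratio of c^(10.5/19).

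| Assumed background change | Spurious rate ratio |
|---|---|
| 10% fall | 0.90^0.553 = 0.943 |
| 20% fall | 0.80^0.553 = 0.884 |
| 10% rise | 1.10^0.553 = 1.054 |
| 20% rise | 1.20^0.553 = 1.106 |

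With categorical month effects the ratio is 1.000 in every row. A 20% fall would show as an 11.6% reduction, over half of the 20% target.

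**5. Precision.** The SE ratio is 0.00563/0.00837 = 0.67. Simulation assumed a facility SD of 0.3 and a monthly residual SD of 0.2 to 0.4, both on the log-rate scale. Type I error under the literal coding was 19% to 60% for a 10% fall and 66% to 100% for a 20% fall, against about 5% with month effects.

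These checks work on facility-month cells and omit the resident random effect. That effect cannot make crossover time vary within a facility.

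**The case against.** The strongest answer is that the section names calendar time as a fixed effect separate from the intervention, and that the crossover times can be read as the set of dates that divide the trial into periods. One facility crosses each month, so those periods are the calendar months with only months 19 and 20 merged. This coding removes the trend almost completely (0.007 months left). The power match also points to period effects as the intention. Both points stand. A reader might infer that the primary analysis is a deliberate before-after comparison, or that no reading of the text adjusts for month. The document supports neither.

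The period reading does not rescue the wording. Calendar periods do not depend on whether a site crossed on schedule, so the clause beginning with irrespective would have no content, nor would a supporting analysis that substitutes actual crossover dates. Both make sense only for a facility-specific variable.

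A second objection is that the drift sizes are assumed. That also stands. A reader might take the 20% target as something background decline could produce on its own. That needs a fall of 1 − 0.8^(1/10.5) = 2.1% per month, about 33% over 19 steps, and nothing in the article suggests it. The one directional trend it cites is a rise, which would hide benefit. Seasonal swings are cyclical, and the linear calculation does not describe them.

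Third, an analysis plan is promised and may code time correctly. That limits what can be said about the eventual analysis. But the protocol does not leave the term open; it defines it twice.

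**Conclusion.** The definition of the time term is wrong as written. Programmed literally, it gives a primary estimate that carries 10.5 months of any linear trend, with a standard error about 0.67 of the month-adjusted one. The gap follows from the schedule alone. The rate ratios of about 0.94 and 0.88 rest on assumed falls of 10% and 20%, and the SE ratio on the planning inputs.

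The analysis text, read literally, also conflicts with the design calculation: 98.9% power against the stated 82%, which month effects reproduce at 81.8%. That comparison rests on treating rates as proportions, a two-sided 0.05 test and exclusion of the transition month. It indicates that month adjustment was probably intended. The finding is therefore a mis-specified definition of the key confounder in the primary model. It is not evidence that the trial will go unadjusted.

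**What to change.** In the protocol, and in the analysis plan if it repeats the text:

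1. State the fixed effects as calendar month of observation (categorical, months 1 to 20) and intervention.
2. State that the intervention indicator follows the randomised crossover schedule (intention-to-treat), and that the supporting analysis sets this indicator by actual crossover dates. Calendar month is the same in both.
3. Delete the parenthesis after calendar time and the statement that calendar time will be the randomised crossover times.

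The cost is wording only. The standard error is larger than under the literal text, but it is the one that matches the stated 82% power, so the sample size does not change.

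### The primary mixed model has no facility-by-month variation, so its standard error is too small if facilities' relative rates shift during the 20 months

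*Protocol article*

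**What the plan says.** The section Statistical analysis sets out the primary model: "DDDs will be measured at the patient level monthly and analysed using a generalised linear mixed model for count data". The fixed effects are intervention and calendar time. The random part is "two random effects, one for variation among RACFs and a second to accommodate repeated measures over time on participants". No facility-by-month term, facility-level autocorrelation or robust variance is mentioned. For the primary test, a *P* "value less than 0.05 will be considered statistically significant". Further detail is referred to an SAP, which was not available here.

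The section Sample size states that "18 RACFs will provide 82% power to detect a 20% reduction in DDDs", based on "a mean cluster size of 50 residents and a control event rate of 120 DDDs per 1000 resident days", one ICC of 0.012 and a coefficient of variation of 0.3. It gives no correlation between different months in the same facility.

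The section on the Needs Assessment Toolkit makes the bundle facility-specific: "Based on the NAT results, appropriate interventions will be selected from the AMS ENGAGEMENT bundle at each facility".

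**The concern.** Only one facility crosses over each month, so the intervention effect is estimated from how facilities' rates move relative to each other over time. A facility effect that is constant over time removes stable differences between facilities. The calendar-time effects remove movements common to all. Neither removes a change specific to one facility for a month or a season. The participant effect does not help, because it is specific to one resident and cannot represent something that raises prescribing for all residents of a facility in the same month. Even if the participant term carried a time structure, it would still act at resident level.

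The article itself makes such changes plausible. Other prescribing-related education is left unrestricted (Exploratory outcome measures), and the section on retention of sites expects COVID-19 effects and changes of management. When the model has nowhere to put this variation, residents in the same facility-month count as more independent than they are. The confidence interval is then too narrow and the *P* value too small, in the analysis that carries the trial's main claim.

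**Working it through.** **1. Layout.** From Randomisation of RACFs and Statistical analysis: 18 facilities, 20 months, one facility per step, transition months excluded. Facility *i* is in control for months 1 to *i*, in transition in month *i*+1 and in intervention afterwards. This leaves 360 − 18 = 342 facility-months, 171 control and 171 intervention.

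**2. The plan's own power.** Control rate 0.120 per resident-day; a 20% reduction gives 0.096; difference 0.024; mean 0.108. Variance at the mean rate is 0.108 × 0.892 = 0.09634. Facility variance is 0.012 × 0.09634 = 0.001156. Residual variance of a facility-month mean is 0.988 × 0.09634 / 50 = 0.001904. Generalised least squares with fixed month effects and one random facility effect gives SE = 0.00837. Power = Φ(0.024/0.00837 − 1.96) = 81.8%, against the stated 82%. Nearby variants give similar values (for example 83.0% with Poisson variance at the mean rate and transition months kept). The match therefore suggests, but does not prove, that planning also used a constant facility effect.

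**3. Error rate when facility-month variation exists.** Scale the total variance to 1, with ICC 0.012, and let the facility autocorrelation be *r*.

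- Fitted covariance of the monthly means of a facility: V = 0.012 J + (0.988/m) I, where J is a matrix of ones and I the identity.
- True covariance: S = 0.012 r J + [0.012(1 − r) + 0.988/m] I. For decay, the first part has entries 0.012 × 0.95^|j−k| for months j and k, and the facility-month term is dropped.
- Model variance: the intervention element of A⁻¹, with A = Σ Z′V⁻¹Z. True variance of the same estimator: that element of A⁻¹(Σ Z′V⁻¹SV⁻¹Z)A⁻¹.
- Type I error = 2[1 − Φ(1.96 × SE_model/SE_true)].

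With m = 50 the residual part is 0.988/50 = 0.01976. At *r* = 0.8 the omitted part is 0.012 × 0.2 = 0.0024, about 12% of it.

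| Residents | Facility autocorrelation (assumed) | SE_model/SE_true | Type I error |
|---|---|---|---|
| 50 | 1 | 1.000 | 5.0% |
| 50 | 0.9 | 0.976 | 5.6% |
| 50 | 0.8 | 0.953 | 6.2% |
| 50 | 0.5 | 0.893 | 8.0% |
| 50 | decay 0.95 per month | 0.785 | 12.4% |
| 100 | 0.9 | 0.947 | 6.3% |
| 100 | 0.8 | 0.902 | 7.7% |
| 100 | 0.5 | 0.798 | 11.8% |

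Example: *r* = 0.8, m = 50 gives 1.96 × 0.953 = 1.867 and 2[1 − Φ(1.867)] = 6.2%. If the fitted model puts the omitted variance into the resident-level residual instead of the facility effect, the first three inflated rows become 5.6%, 6.3% and 8.2%. The 100-resident rows matter because 50 is the eligibility minimum. They also stand in for 50 residents with a within-resident correlation of 0.5, since 0.988 × 0.5/50 = 0.988/100; a direct calculation of that case gives 6.4%, 7.7% and 11.8%.

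**4. Power with the term included.** Replacing V by S (m = 50, scale of step 2) gives SE = 0.00858, 0.00876 and 0.00917, and power of 79.9%, 78.2% and 74.5% at *r* = 0.9, 0.8 and 0.5.

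**Approximations.** Linear model on facility-month means, variance components known, normal reference distribution.

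**The case against.** The strongest reply is that the protocol gives no facility-month variance, so nothing shows that the error rate will be missed. At the planned ICC and cluster size with high autocorrelation, the excess is about one percentage point or less. This stands as to size: the result is conditional, and the 12% figure needs a decay under which months 19 apart correlate at only 0.95^19 ≈ 0.38, which no passage supports or excludes. It does not remove the point, because every setting with non-zero omitted variance errs in the same direction.

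A second reply is that the unseen SAP may settle this. It may add a robust variance, but the article already states the random-effects structure and counts its terms, so this is a choice made and not a detail deferred.

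Three stronger readings are tempting and not supported:

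- **Plain Poisson.** A reader might infer far larger inflation from an equidispersed Poisson model. The article says only that the model is for counts. Such a model also conflicts with the planning values: 120 per 1000 days is about 3.65 DDDs per month, so the relative variance is 1/3.65 = 0.27, and with coefficient of variation 0.3 the ICC would be 0.09/(0.09 + 0.27) = 0.25, about 20 times the stated 0.012.
- **Reference distribution.** A reader might add inflation from a normal critical value with few clusters. The article states neither a critical value nor a degrees-of-freedom method.
- **Tailored bundle.** A reader might infer that effects differing by facility break the 5% level. The section Study hypothesis defines the null as no change due to the intervention. If the bundle does nothing in any facility, there is no effect variation. Tailoring affects the interval for the average effect, and one average effect of offering a tailored bundle is a legitimate target.

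**Conclusion.** The point holds in conditional form and should be fixed. The stated random effects keep the 5% level only if facilities' relative rates are constant apart from common month effects. At the protocol's ICC of 0.012 and 50 residents, the actual level is about 5.6% to 8.0% for autocorrelation 0.9 to 0.5, and about 12% under 0.95-per-month decay. With 100 residents it is about 6.3% to 11.8% for autocorrelation 0.9 to 0.5. The autocorrelations are assumptions; the direction is not. The documents do not support saying that the level is certainly missed, or that the inflation is large at the planning values.

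**What to change.** Before database lock, add to the primary model either a random facility-by-month effect or a facility-level autoregressive or decaying correlation. Alternatively, keep the two random effects and use a cluster-robust variance, which avoids estimating another variance component from 18 facilities. Either way, specify a small-sample correction for 18 clusters.

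Add a random facility-by-intervention effect as a sensitivity analysis, described as addressing the width of the interval for the average effect.

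Restate the power over a range of autocorrelations: 79.9%, 78.2% and 74.5% at 0.9, 0.8 and 0.5 in place of a single 82%.

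The cost is a few lines of specification and SAS code, somewhat wider intervals and a lower stated power. If the random intervention effect were moved into the primary model, power would be about 77.2% or 65.3% for an assumed effect SD of 10% or 20% of the control rate (no facility-month variation added), which is a reason to keep it as a sensitivity analysis.
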